# Transanal minimally invasive surgery (TAMIS) versus endoscopic submucosal dissection (ESD) for resection of non-pedunculated rectal lesions (TRIASSIC study): study protocol of a European multicenter randomised controlled trial

**DOI:** 10.1186/s12876-020-01367-z

**Published:** 2020-07-13

**Keywords:** Endoscopic submucosal dissection, Transanal minimally invasive surgery, Rectal cancer, Adenoma

## Abstract

**Background:**

In the recent years two innovative approaches have become available for minimally invasive *en bloc* resections of large non-pedunculated rectal lesions (polyps and early cancers). One is Transanal Minimally Invasive Surgery (TAMIS), the other is Endoscopic Submucosal Dissection (ESD). Both techniques are standard of care, but a direct randomised comparison is lacking. The choice between either of these procedures is dependent on local expertise or availability rather than evidence-based. The European Society for Endoscopy has recommended that a comparison between ESD and local surgical resection is needed to guide decision making for the optimal approach for the removal of large rectal lesions in Western countries. The aim of this study is to directly compare both procedures in a randomised setting with regard to effectiveness, safety and perceived patient burden.

**Methods:**

Multicenter randomised trial in 15 hospitals in the Netherlands. Patients with non-pedunculated lesions > 2 cm, where the bulk of the lesion is below 15 cm from the anal verge, will be randomised between either a TAMIS or an ESD procedure. Lesions judged to be deeply invasive by an expert panel will be excluded. The primary endpoint is the cumulative local recurrence rate at follow-up rectoscopy at 12 months. Secondary endpoints are: 1) Radical (R0-) resection rate; 2) Perceived burden and quality of life; 3) Cost effectiveness at 12 months; 4) Surgical referral rate at 12 months; 5) Complication rate; 6) Local recurrence rate at 6 months. For this non-inferiority trial, the total sample size of 198 is based on an expected local recurrence rate of 3% in the ESD group, 6% in the TAMIS group and considering a difference of less than 6% to be non-inferior.

**Discussion:**

This is the first European randomised controlled trial comparing the effectiveness and safety of TAMIS and ESD for the *en bloc* resection of large non-pedunculated rectal lesions. This is important as the detection rate of these adenomas is expected to further increase with the introduction of colorectal screening programs throughout Europe. This study will therefore support an optimal use of healthcare resources in the future.

**Trial registration:**

Netherlands Trial Register, NL7083, 06 July 2018.

## Background

Colorectal cancer (CRC) has the second highest incidence rate of all cancers in Europe with an annual incidence rate of approximately 500.000 of which 175.000 are located in the rectum [1].. Since the introduction of population based screening, CRCs are more often detected at an earlier disease stage than symptom-detected CRCs [2]. Resection of pre-malignant precursors has shown to lower the mortality rate due to CRC by 50% [3]. Along with the clearly benign polyps and clearly invasive cancers, colorectal cancer screening also detects many lesions in the act of progressing from one to the other. These lesions present a diagnostic challenge and complex clinical decision making to avoid overtreatment with unnecessary mortality and morbidity on the one hand but also undertreatment on the other. This dilemma is most acute for rectal lesions where standard surgical resection techniques are associated with higher rates of mortality and serious morbidity, such as a permanent stoma and sexual dysfunction, which can be avoided by organ sparing techniques [4].

Ideally, preoperative staging would allow for accurate prediction of invasive cancer and the chance of local lymph node metastases. Unfortunately, current preoperative staging is far from perfect. This is true for all available staging modalities (MRI, endoscopic ultrasound, advanced optical endoscopic imaging) both individually and in combination. This has been shown by a previous randomised study of organ sparing treatment of rectal polyps, the TREND study: 13% of the lesions preoperatively staged as benign turned out to be malignant [5]. Currently most lesions that are not overtly cancerous on endoscopic inspection are resected by piecemeal Endoscopic Mucosal Resection (pEMR) in Western countries. However, piecemeal resection has an important disadvantage in that it prevents optimal histological assessment. This can make histological distinction between a benign and a malignant lesion impossible leading to unnecessary surgical resections or to under staging and undertreatment. The safety and feasibility of *en bloc* resections in the rectum, combined with the limitations of preoperative staging are leading to a shift away from pEMR to *en bloc* resection of large lesions in the rectum. Furthermore, a recent cost-effectiveness analysis suggests that an *en bloc* resection strategy might also be cheaper than a piecemeal resection strategy for rectal lesions by reducing the numbers of patients requiring additional radical rectal surgery [6].

Lesions can be removed *en bloc* with a flexible endoscope by Endoscopic Submucosal Dissection (ESD). ESD results in high *en bloc* rates and low recurrence rates of around 2% [7]. However, ESD has longer procedure times, is difficult to perform and associated with relatively high rates of perforation (5%) [8]. Fortunately, the clinical consequences of perforation in the rectum are usually limited and can almost always be treated conservatively. Several surgical techniques are also available for local *en bloc* resection of large non-pedunculated rectal lesions. Such as Transanal Endoscopic Micosurgery (TEM) or Transanal Minimally Invasive Surgery (TAMIS). The TAMIS technique has largely superseded classical TEM since it requires minimal investment in specialised equipment. Here the lesion is removed transanally with the use of a silicon-rubber port and standard laparoscopic instruments. Compared to ESD it also has a relatively short learning curve, short procedure times and is financially well compensated.

No reports have been published comparing TAMIS and ESD directly. Two recently published meta-analysis comparing TAMIS/TEM to ESD concluded a similar rate of adverse events, recurrence rate and *en bloc* resection rate [9, 10]. Regarding the procedure and hospitalization duration both papers came to a different conclusion. The first concluded that ESD was associated with shorter procedure times and duration of hospitalization [10], the second concluded that there was no difference [9]. However, both meta-analyses largely included ESD procedures that were conducted in Asian countries. As a result the findings may not be representative for the daily practice in the West where the results of ESD tend to be inferior. The aim of the TRIASSIC study is to perform a multicentre, randomised controlled study comparing ESD to TAMIS for the *en bloc* removal of large non-pedunculated rectal lesions in a Western population. This is important as the detection rate of these lesions has increased greatly with the introduction of screening programs. This study will enable the optimal use of healthcare resources in the future.

## Methods/design

### Hypothesis

We hypothesise that ESD will lead to non-inferior recurrence rates in lesions that prove to be benign. We hypothesise that TAMIS will have a higher R0 resection rate for lesions that prove to be invasive but that this will not translate to a reduced need for additional surgery. We further hypothesise that ESD will lead to less serious complications than TAMIS and lower societal costs.

### Objective

The primary aim of this study is to compare both procedures with regard to local recurrence rates at 12 months. The secondary aims are to compare costs, complication rates and the burden perceived by patients in both the short and long term between the two procedures.

### Design

This will be a multicentre randomised non-inferiority trial comparing TAMIS and ESD in patients with large rectal lesions. The flowchart of the design of the TRIASSIC study is shown in Fig. 1.

**Fig. 1 Fig1:**
[figure not shown]
Flowchart of the TRIASSIC study. *Abbreviations:* TAMIS: Transanal Minimally Invasive Surgery, ESD: Endoscopic Submucosal Dissection

### Randomisation

Patient data will be entered into a cloud-based electronic data capture system (Castor). This system will randomise patients to either the TAMIS or the ESD group. Stratification will take place for the distance of the lesion to the dentate line and lesion size.

### Blinding

Blinding was deemed unfeasible for this trial since both procedures are very different in nature, performed by different specialists and require different associated care facilities within the hospital.

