#### Follow-up

The follow-up consists of a rectoscopy performed 6 and 12 months after the TAMIS/ESD by an endoscopist trained in advanced endoscopic imaging techniques. Three white light pictures, 3 enchanced imaging pictures and preferably a short video should be taken of the scar. In case of no visible recurrence 3 biopsies of the scar should be taken. In case of visible benign recurrence an attempt at an endoscopic resection will be performed, or a re-TAMIS. If recurrence is found at the 12-month rectoscopy this will be resected and further surveillance will be planned for 6 months later.

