#### Central pathology revision

All resection specimens will be revised centrally by an expert pathologist.

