### Outcomes

#### Primary study endpoint (for non-inferiority)

Cumulative recurrence rate at follow-up rectoscopy after 12 months, histologically confirmed from resected visible residual disease or, if not present, from biopsies of the scar

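### Blinding is ruled out for the whole trial on grounds that reach only patients and operators, and no masked read is provided for the follow-up histology that defines the primary endpoint

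*Protocol article*

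**What the plan says.** All places are in the protocol article.

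- **Blinding.** The decision covers the trial as a whole: "Blinding was deemed unfeasible for this trial since both procedures are very different in nature". The remaining grounds are that the procedures are "performed by different specialists and require different associated care facilities within the hospital". No exception is made for anyone who assesses outcomes.
- **Primary study endpoint.** Recurrence is "histologically confirmed from resected visible residual disease or, if not present, from biopsies of the scar".
- **Follow-up.** Rectoscopy at 6 and 12 months is done "by an endoscopist trained in advanced endoscopic imaging techniques". Whether this person is masked, or independent of the treating team, is not stated. Where nothing is seen, tissue is still sampled: "In case of no visible recurrence 3 biopsies of the scar should be taken". Pictures are also required ("Three white light pictures, 3 enchanced imaging pictures and preferably a short video should be taken of the scar"), but no reader is named for them and they have no role in the endpoint.
- **Central pathology revision.** "All resection specimens will be revised centrally by an expert pathologist". Scar biopsies are not named and masking is not mentioned.
- **Sample size calculation.** Assumed recurrence is 3% (ESD) and 6% (TAMIS), with a 6% margin, one-sided 97.5% confidence and 80% power. This gives 166 evaluable patients and 198 in total after allowing for 4% lost to follow-up and 12% with additional surgery. **Data-analysis** gives the margin as 3%, tested with a one-sided Mantel-Haenszel test at 0.025.

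**The concern.** The three grounds (procedure, specialist, facility) describe what patients and operators experience. A follow-up biopsy reaches the pathology laboratory months later, and what the request form says about the index procedure is a matter of choice. The conclusion in the Blinding section is therefore wider than its reasons.

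This matters because the primary endpoint is a histological call. With assumed recurrence of 3% to 6%, most patients should have no visible recurrence, so their outcome rests on scar biopsies. That is the tissue the central revision section does not name. If equivocal tissue were read differently by arm, the error would enter the primary difference directly, in a trial where a handful of events decides the result. Neither the article's sample size nor its analysis protects against this. Masking the reader does.

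**Working it through.** **1. The plan's own figure.** Inputs from Sample size calculation: p(ESD) = 0.03, p(TAMIS) = 0.06, margin 0.06, one-sided alpha 0.025, power 0.80.

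- Variance term: 0.03 × 0.97 + 0.06 × 0.94 = 0.0291 + 0.0564 = 0.0855.
- Distance to the margin: 0.06 + (0.06 − 0.03) = 0.09.
- n per arm = (1.960 + 0.842)² × 0.0855 / 0.09² = 82.8, so 83 per arm and 166 in total.
- Inflation for 16% not assessable: 166 / 0.84 = 197.6, so 198.

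Both stated numbers reproduce. Power at 83 per arm is 80.1%.

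**2. How few events carry the result.** Expected recurrences are 83 × 0.03 = 2.5 (ESD) and 83 × 0.06 = 5.0 (TAMIS). One patient is 1/83 = 1.2 percentage points, or 1.2/6 = one fifth of the 6-point margin.

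**3. Where one patient flips the conclusion.** Take 5 TAMIS events (the expected number), 83 per arm, and vary the ESD events x. The Wald upper limit is (x − 5)/83 + 1.96 × SE, with SE² = [a(1 − a) + c(1 − c)]/83, a = x/83 and c = 5/83. The score test uses the restricted maximum-likelihood variance.

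| Margin | Method | Last ESD count that passes | First that fails |
|---|---|---|---|
| 6% | Wald | 4 (upper limit 5.7%) | 5 (7.2%) |
| 6% | Score | 3 (one-sided p = 0.014) | 4 (p = 0.033) |
| 3% | Wald | 2 (upper limit 2.5%) | 3 (4.1%) |
| 3% | Score | 1 (p = 0.009) | 2 (p = 0.026) |

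As an example, Wald with x = 4 gives −0.0120 + 1.96 × 0.0351 = 0.0568. In each row one reclassified ESD patient at the boundary changes the conclusion, but the boundary moves with the method and the margin. The planned stratified Mantel-Haenszel test is neither of these two, so the exact count under the plan is not determined here.

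**4. Illustration of differential reading.** The error rates are assumed and do not come from the documents. At the 6% null (ESD 12%, TAMIS 6%, 83 per arm), suppose a share of ESD recurrences alone is missed. The chance of falsely declaring non-inferiority (normal approximation, with the exact binomial probability for the Wald rule in brackets) is:

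- none missed: 2.5% (3.0%)
- 10% missed: 4.7% (5.5%)
- 20% missed: 8.4% (9.7%)
- 30% missed: 14.4% (16.3%)

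The error can also run the other way. At the planned rates, false positives of 1%, 2% or 3% in ESD alone lower power from 80% to 66%, 52% and 38%.

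**The case against.** The strongest reply is that this is a condensed article. Request-form content and slide routing normally sit in the full protocol, so silence on them is no fault. That is right as far as silence goes. The Blinding section is not silent, however: it states a trial-wide decision and gives reasons, and the reasons do not carry it as far as the pathologist.

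Several stronger readings are tempting, and the documents do not support them:

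- **That readers are known to be unmasked, or that biopsies get one local read.** The article says neither. It follows at most by inference from the unqualified blinding statement.
- **That scar images decide the endpoint.** They do not; histology does. The endoscopist's view determines which tissue is taken, and a scar judged clear is still biopsied, which backs up a lenient visual call.
- **That recurrence tissue lacks central review.** Resected visible disease may fall under the central revision of resection specimens, although that section may equally mean index specimens only. The clear gap is the scar biopsies.
- **That noise or leniency favours non-inferiority.** This is not general here. The plan assumes ESD is better, so equal under-reading in both arms would shrink the assumed ESD advantage, and false positives in ESD cost power. No section indicates which way a reader would lean.
- **That a move from 4 to 3 ESD events turns failure into success.** This holds for a score test at the 6% margin, not for a Wald interval and not at 3%. Any decision rule has some one-event boundary.

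It also stands that the live endoscopist would be hard to mask, because a full-thickness or sutured TAMIS scar might show which procedure was done. The point is therefore confined to histology.

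**Conclusion.** The point holds in its narrow form. Blinding is excluded for the whole trial on grounds that apply to patients and operators, and no masked read is stated for the follow-up histology that defines the primary endpoint, scar biopsies above all. This leaves open an avoidable route for bias. It does not show that bias is present or in which direction it would act.

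The route matters because about 2.5 and 5 events are expected, so one case is worth 1.2 points and can tip a result that lies at the boundary. These figures rest on the article's assumed rates and 83 evaluable patients per arm. The flipping count also depends on the test and on which margin applies; the 6% and 3% statements must be reconciled in any case. This is a worthwhile, inexpensive improvement and not a fatal flaw. If follow-up readers are already masked under the full protocol, one sentence in the Blinding section settles it.

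**What to change.** 1. Limit the Blinding section to patients and operators, and state that pathologists reading follow-up tissue are masked to arm.
2. Submit the 6- and 12-month scar biopsies and any recurrence tissue under study number, without naming the index procedure.
3. Use that masked read for the primary endpoint. The central pathologist already in the trial, also masked to arm, may settle equivocal cases, by the same rule in both arms.

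**Cost.** A change of protocol and request-form wording, and slightly more slide handling. No added staff, visits or procedures are needed, and the sample size stays at 166 evaluable and 198 in total. Masking may be imperfect where deeper recurrence tissue reveals the earlier procedure; recording such cases would let their number be reported.

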### Study population

In order to be eligible to participate in this study, a subject must meet all of the following **inclusion criteria**:
Non-pedunculated lesion > 2 cm in the rectum where the bulk of the lesion is below 15 cm from the anal verge found at endoscopy≥18 years oldWritten informed consent

A subject is not eligible for inclusion in case of presence of any of the following **exclusion criteria**:
Features of advanced disease or deep-submucosal invasion at optical endoscopic evaluation*Features of advanced disease on cross-sectional imaging*Prior endoscopic resection attemptThe risks of treatment are felt to exceed the benefits.

** Where there is discordance in the results, the optical endoscopic evaluation will be given the most weight and the case discussed by an expert panel.*

### Intervention strategies

#### Transanal minimally invasive surgery (TAMIS)

This procedure was first described by Atallah et al. [11]. The procedure will be performed under either general or spinal anaesthesia at the discretion of the anaesthetist. For this trial only the GelPOINT® path transanal access platform will be used. This is to ensure the greatest possible uniformity in procedures and was already being used by the vast majority of surgeons prior to the study. After insertion of the instruments the margins of the lesion may be marked with coagulation dots to facilitate the incision at the lesion margins at the discretion of the surgeon. The incision must be placed at a distance of at least 5 mm around the border of the lesion to prevent thermal damage complicating the histological assessment. If a lesion is very distal (i.e., at or just above the dentate line), the distal margin can be incised using standard transanal retractors and electrocautery. Before the start of the lateral or proximal portion of the dissection, the TAMIS port can be inserted to be used for the remainder of the dissection. Ideally a partial thickness resection of the lesion will be performed following the intramuscular plane of the muscularis propria using a diathermic hook but a full thickness resection may be performed at the discretion of the surgeon. The wound may be closed, if required, with laparoscopic suture material in a transverse direction so as not to narrow the lumen of the rectum. The type of sedation and precise instruments will be noted in the CRF. Pneumorectum will be achieved using CO2 for insufflation. Initial pressure settings should be between 12- and 20-mmHg and can be increased if there is difficulty in maintaining distension for visualisation. An anal block with bupivacaine or ropivacaine bilaterally is recommended. All other aspects of the procedure and post-procedural care are at the discretion of the operator.

#### Endoscopic submucosal dissection (ESD)

After insertion of the endoscope the margins of the lesion may be marked with coagulation dots to facilitate the incision at the lesion margins at the discretion of the endoscopist. The lesion will be ‘lifted’ by injection of fluid into the submucosa. The choice of injection fluid is at the discretion of the operator. A partial or full circumferential incision will be made around the lesion (at the discretion of the operator) at a distance of at least 5 mm from the border of the lesion to prevent thermal damage complicating the histological assessment. Dissection will take place in the submucosal layer underneath the specimen just above and parallel to the underlying muscularis propria layer. The choice of ESD knife is at the discretion of the operator and must be recorded in the CRF. All procedures will be performed with a high-resolution magnifying video- endoscope. The procedure will be performed under sedation, not general anaesthesia. The choice of sedation technique is at the discretion of the endoscopist but Propofol sedation is recommended. In the case of intraprocedural perforation, this will be treated using clips and desufflation of the peritoneal cavity if required, with an intravenous cannula. In the case of minor bleeding from a small vessel, contact coagulation with the tip of a knife or coagulation with haemostatic forceps will be used for haemostasis. In cases of a severe bleeding from a large vessel or artery, haemostatic forceps will be used for haemostasis. If a pulsating large vessel is exposed within the resection wound, clipping can be performed to prevent delayed bleeding. All of this is considered standard care and should be mentioned in the CRF. All other aspects of the procedure and post-procedural care are at the discretion of the operator.

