#### * complications are defined as follows

*Intraprocedural peritoneal breach: the condition in which the abdominal cavity is visible from the colorectal lumen during the procedure because of mural tissue defects, that requires* (1) *(prolonged) admission or* (2) *surgery**Intraprocedural bleeding: bleeding that occurs during the procedure that cannot be controlled by standard local haemostasis techniques such as electrocoagulation or clips and that requires* (1) *transfusion or* (2) *termination of the TAMIS or ESD procedure.**Postprocedural bleeding: bleeding within 30 days after the procedure resulting in* (1) *new presentation at the hospital,* (2) *hospital admission, transfusion* (3) *or* (4) *repeated intervention to obtain haemostasis.**Postprocedural bowel perforation: a bowel perforation within 30 days after the procedure that is detected after completion of the procedure during which a peritoneal breach did not occur, diagnosed by abdominal pain with focal guarding and a rise in C-reactive protein and/or fever (T > 38.5 C) in combination with free air in the peritoneal cavity at abdominal CT.**Postprocedural serositis: abdominal pain with focal guarding and/or fever (T > 38.5 C) within 30 days after the procedure, but without signs of perforation (free air at abdominal CT) and in the absence of another infection focus (urinary, pulmonary* etcetera*) that requires (prolonged) admission*

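### A perforation recognised during either procedure without a view into the abdominal cavity can fit none of the five complication definitions, so the overall complication rate can be understated

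*Protocol article*

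**What the plan says.** All references are to the protocol article.

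- **Endoscopic submucosal dissection (ESD):** "In the case of intraprocedural perforation, this will be treated using clips and desufflation of the peritoneal cavity if required, with an intravenous cannula". After describing the handling of bleeding as well, the section adds: "All of this is considered standard care and should be mentioned in the CRF".
- **Secondary study endpoints:** the overall complication rate is marked with an asterisk that leads to a list of five defined complications.
- **Complication definitions, wall injury during the procedure (termed a breach):** this is defined as "the condition in which the abdominal cavity is visible from the colorectal lumen during the procedure because of mural tissue defects". It counts only if (prolonged) admission or surgery is needed.
- **Complication definitions, postprocedural bowel perforation:** a perforation within 30 days "that is detected after completion of the procedure during which a peritoneal breach did not occur", diagnosed by symptoms together with free air on CT.
- **Complication definitions, the other three:** intraprocedural bleeding, postprocedural bleeding, and serositis. Serositis requires that CT shows no free air.
- **Background:** gives a perforation rate of 5% as a drawback of ESD, and says that "the clinical consequences of perforation in the rectum are usually limited and can almost always be treated conservatively".
- **Hypothesis:** "We further hypothesise that ESD will lead to less serious complications than TAMIS and lower societal costs".
- **Transanal minimally invasive surgery (TAMIS):** the preferred plane is intramuscular, but the surgeon may resect the full thickness of the wall.

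**The concern.** The ESD section speaks of perforation, with gas in the peritoneal cavity as a possible consequence. The endpoint list speaks of a peritoneal breach, and defines it by what the operator can see. These are different events. A small defect that is recognised and closed at once may never give a view into the cavity. It is then not a breach, and because it was found during the procedure it is not a postprocedural perforation either.

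The visibility condition is separate from the severity condition. The definition already limits itself to clinically relevant events by requiring (prolonged) admission or surgery. Visibility describes how the defect looked, so it can exclude events that pass the protocol's own test of relevance.

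What is at stake is the secondary safety comparison, about which the Hypothesis section makes a directional statement. The primary endpoint and the sample size are not affected.

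**Working it through.** **1. The definitions set against one event.** Take a perforation recognised and treated during the procedure, with the abdominal cavity not seen, followed by (prolonged) admission or surgery.

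| Item | Deciding condition | Met? |
|---|---|---|
| Intraprocedural peritoneal breach | Cavity visible, and (prolonged) admission or surgery | No: cavity not visible |
| Intraprocedural bleeding | Bleeding | No |
| Postprocedural bleeding | Bleeding | No |
| Postprocedural bowel perforation | Detected after completion; symptoms and free air on CT | No: detected during the procedure |
| Postprocedural serositis | Guarding and/or fever, no free air on CT, (prolonged) admission | Not if CT shows free air or if there are no such symptoms |

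The event is counted only if symptoms develop, CT shows no free air and admission is required. It then counts as serositis, a category meant for patients without signs of perforation.

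**2. Arm size (the plan's own figure).** Inputs from Sample size calculation: recurrence 3% (ESD) and 6% (TAMIS), margin 6%, one-sided alpha 0.025, power 80%, non-evaluable 4% + 12% = 16%.

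n per arm = (1.960 + 0.842)² × (0.06 × 0.94 + 0.03 × 0.97) / (0.06 + 0.03)² = 7.849 × 0.0855 / 0.0081 = 82.85, so 83 per arm and 166 evaluable. Then 166 / 0.84 = 197.6, so 198 in total and 99 per arm. This matches the article. It is used here only for the arm size.

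**3. Events exposed to the gap in the ESD arm.** At the Background's 5%:

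- Expected perforations: 99 × 0.05 = 4.95. The central 95% binomial range is 1 to 10.
- Chance of at least one: 1 − 0.95^99 = 99.4%.

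The uncounted share f is the share of perforations recognised during the procedure, without a visible cavity, with a qualifying consequence, and not counted as serositis. The article does not give it, so these values are assumptions:

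| f (assumed) | Uncounted ESD events, 4.95 × f | Understatement of ESD rate (points), 5 × f |
|---|---|---|
| 0% | 0 | 0 |
| 25% | 1.2 | 1.25 |
| 50% | 2.5 | 2.5 |
| 75% | 3.7 | 3.75 |
| 100% | 5.0 | 5.0 |

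If 25% have no visible cavity and half of those have a qualifying consequence (both assumed), the count is 4.95 × 0.25 × 0.5 = 0.6 events.

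**4. Effect on the comparison.** Let t be the TAMIS rate of wall injuries left uncounted by the same wording. The article gives no such rate. The net shift in favour of ESD is 5 × f − t, in percentage points. With f = 50%, t = 0 gives +2.5, t = 2.5 gives 0, and t = 5 gives −2.5. The sign depends on a figure that is not available.

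**The case against.** The strongest stronger reading is that the wording tilts the safety comparison towards ESD. A reader might infer this because perforation is named as an ESD harm and the authors expect fewer serious complications with ESD. The documents do not support it. The definitions are the same in both arms, TAMIS may go through the full wall, and no TAMIS rate is given. Nor does any section say that peritoneal entry is more readily seen in TAMIS; ESD too is done under high-resolution video endoscopy.

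Other points on that side:

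- **The event is not lost.** The ESD section asks for it in the CRF, so it could be reported separately. This stands for reporting, but a CRF entry does not place the event in an endpoint defined by the list. Reclassifying it later would be done in an unblinded trial.
- **The postprocedural item might be stretched.** If pain, raised C-reactive protein and/or fever, and free air first come together after the procedure, one could argue that detection happened then. That reading is possible. The fact that the case is arguable is itself a reason to settle it in the definition.
- **Part is caught elsewhere.** Some cases without free air qualify as serositis, and referral for trans-abdominal surgery is a separate endpoint. Both points stand and narrow the gap.
- **The limit to clinically relevant events looks deliberate.** It agrees with the Background's remark on limited consequences. That justifies the admission-or-surgery condition. It does not justify the visibility condition.
- **The 5% is a ceiling for this purpose.** It covers perforation generally, including cases found later, and limited consequences mean that many would not meet the admission or surgery test. This stands: no floor above zero can be defended.

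**Conclusion.** The gap is real on the text. A perforation recognised during either procedure without a visible cavity can lead to (prolonged) admission, surgery, or symptoms with free air on CT and still meet none of the five definitions. The overall complication rate can therefore be understated.

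If the cited 5% applies to this trial, the understatement of the ESD rate lies between near 0 and about 5 percentage points in expectation (at most about 5 of 99 patients). The upper end assumes that every perforation falls in the gap, which is unlikely. The ESD arm may be affected more, but neither the direction nor the size of any bias between the arms is established. The point concerns one secondary endpoint. It deserves correction because the remedy is nearly free, not because the comparison has been shown to be skewed.

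**What to change.** Reconcile the terms used in the ESD section and in the complication definitions, and make the two wall-injury items exhaustive under one rule for both arms:

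1. **During the procedure:** count any perforation or extraluminal gas recognised during ESD or TAMIS that meets the existing consequence criteria, (prolonged) admission or surgery, whether or not the abdominal cavity was visible.
2. **Within 30 days:** count symptomatic perforation with free air on CT whenever the perforation was first recognised.
3. **Counting:** count each patient once across the two items.
4. **Full-thickness TAMIS defects:** apply the same consequence criteria. A full-thickness resection without such a consequence is then not an event, and one with it is. Exempting intended TAMIS excisions outright while counting unintended ESD defects would create a new asymmetry.

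This changes what is counted, not how patients are treated. It costs a rewording of the two definitions and one identical CRF item in both arms, unless the CRF already has it. The reported complication rates may become slightly less favourable.
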